### 2.2.2 Inclusion criteria

Healthy full-time employed individuals between the age of 18 and 65, who have a sufficient knowledge of the German language in order to fill in the self-administered questionnaires by themselves.

### 2.2.3 Exclusion criteria

Subjects not giving consent for participation as well as those with movement restrictions, various diseases and accidents within the last three months that affect productivity at the workplace, cannot take part in this study. Furthermore, shift workers and individuals, who are exposed to high-risk explosive environments, will be excluded from participation.

## Instruments

### 2.3.1 Personal and job related factors

For each subject, gender *(male / female)* and employment *(temporary / permanent)* will be assessed as binary variables. Nationality *(Swiss / EU / other)*, marital status *(single / married / divorced)*, and smoking status *(yes / no / never)* will be recorded with three categories, while alcohol consumption *(never / once to several times per month / once to several times per week / once per day),* German skills *(very good / good / medium / bad / very bad)*, highest education *(compulsory school / apprenticeship / higher vocational school / diploma or maturity / university)* and working time model *(flexitime / fix time / shift work / night work / weekend work / short work)* will be evaluated with four, five and six categories, respectively. Age, native language, profession, avocation, medication, illnesses and accidents and working hours will be asked as open questions. Furthermore, to get an overview of the individual work activity, participants will be asked to keep a daily list of the main completed tasks including time information in accordance with the questionnaire regarding professional integration and pension .

### 2.3.2 Classification of occupations

The reported professions will be classified into 9 categories based on the International Standard Classification of Occupations ISCO-88  *(1. Managers and administrators, 2. Professionals, 3. Technicians and associate professionals, 4. Clerks, 5. Service workers, 6. Agricultural and fishery workers, 7. Construction and related workers, 8. Plant and machine operators, 9. Elementary workers)*. These 9 categories will then be collapsed into 3 groups with low, middle and high occupational activity according to Suva experts in the field of ergonomics (*1st group*: Categories 1 (Managers and administrators) and 2 (Professionals); *2nd group*: Categories 3 (Technicians and associate professionals), 4 (Clerks) and 5 (Service workers); *3rd group*: Categories 6 (Agricultural and fishery workers), 7 (Construction and related workers), 8 (Plant and machine operators) and 9 (Elementary workers). Reliability of this stratification has been previously shown .

### 2.3.3 International Physical Activity Questionnaire

The International Physical Activity Questionnaire (IPAQ) represents a convenient and simple instrument for measuring health enhancing physical activity at the population level. The self-administered long version of the IPAQ, being freely available in internet , will be used in the present study. It includes 26 questions and assesses past-week frequency (days) and duration (time per day) of physical activity within the domains of work, leisure-time, transport and domestic & garden. Moreover, each domain consists of walking, moderate and vigorous activities. In addition, daily sitting time at weekdays and weekend days is recorded.

According to the IPAQ guidelines for data analysis , continuous scores in form of MET-minutes per week will be calculated for each domain. MET-minutes per week, defined as energy costs of physical activity, will be computed by multiplying the intensity (specific MET value) of an activity with its frequency (days) and duration (minutes). The corresponding MET values are set by the IPAQ guidelines based on the compendium of physical activity .

According to numerous validity and reliability tests carried out in twelve different countries, the IPAQ is considered as an internationally valid assessment tool with acceptable measurement properties . The long version of the IPAQ was translated into German as part of a dissertation and was validated in an Austrian sample . It could be shown that it is suitable for research purposes with regard to physical activity detection .

### 2.3.4 SF-36

The SF-36 is a general quality of life questionnaire consisting of 36 items, which are formatted as binary questions or as semantic six-point differential scales. It refers to the past four weeks and includes nine content areas concerning vitality, general health perception, physical functioning, social functioning, role limitations (emotional/physical problems), pain, mental health and health change . The SF-36 is considered to be the gold standard for measuring functional status and health-related quality of life and is therefore the most used questionnaire in this context .

Since physical and mental disorders as well as pain may influence activity behaviour, the SF-36 will be used in the present study to adjust for potential confounders.

### 2.3.5 Visual Analogue Scale

The Visual Analogue Scale (VAS) is a measuring instrument for subjective characteristics that cannot be directly measured. Individuals express their response to a VAS item by marking a position along a continuous line between two end-points.

The indicated locus will then be quantified by a defined scale . In epidemiologic and clinical research, the most common VAS is a straight horizontal line of 100 mm length with its ends representing extreme limits of the measured parameter (worst - best) . The VAS score is determined by measuring the distance in mm from the left end of the line to the point marked by the participant. Validity and reliability of VAS have been scientifically tested for a variety of parameters, such as acute and chronic pain .

In this study, individual’s perception of past-week work and non-work related physical exertion and effort will be assessed by 100mm VASs. This may be valuable to evaluate whether the investigated period (exposure time) is representative and reflects a normal week.

### 2.3.6 Borg Scale

The Borg Scale represents a simple method to rate perceived exertion and can be compared to other scales, such as VAS. It is used for various purposes, such as measuring patient’s exertion during a performance test or assessing the intensity of training and competition in athletes .

The original scale developed by Borg ranging from 6 (no exertion at all) to 20 (maximal exertion) was updated and transformed into a combined category-ratio scale CR10 with the ratings 0 (nothing at all) to 10 (very very hard) .

The latter will be used in the present study. Subjects will be instructed to rate their work related physical exertion twice per day, at the end of the morning and in the late afternoon. The indicated Borg value should reflect how heavy and strenuous work feels to them considering all sensations of physical stress, effort and fatigue.

## Measurements

### 2.4.1 Anthropometric measurements

Anthropometric measurements include body height, body weight and waist circumference. Body height will be assessed without shoes by a medical measuring stick to the nearest mm. The measurement of body weight will be performed on subjects in light clothing without shoes by a medical scale with an accuracy of 0.1 kg.

Waist circumference will be determined midway between the lowest rib and the iliac crest according to the Swiss Heart Foundation using a medical measuring tape with a precision of 0.1 cm. The measurement will be carried out on standing subjects after a moderate expiration.

### 2.4.2 20 meter shuttle run

The multistage 20 meter shuttle run is a common endurance fitness test to evaluate the maximal aerobic power of healthy adults . It is simple in use and economical and large groups can be tested at once.

This test will be conducted on a flat, non-slip surface and participants will be instructed to run back and forth between two lines, which are 20 meters apart (Figure 1). Running velocity is determined by intervals between two audio signals emitted by a pre-recorded tape. Subjects have to touch the 20 meter lines simultaneously with the sound of these signals. The initial running velocity is 8.0 km/h. Every minute (stage), the intervals are shortened and speed is increased by 0.5 km/h. The test ends when the subject gives up or when he can no longer keep the pace and does not reach the line in time (> 3 metre away from the 20 meter line) twice in a row.

**Figure 1:** Schematic illustration of the 20 meter shuttle run

The test result corresponds to the number of reached stages. According to a given table , this score is used to predict maximal oxygen uptake (VO2max), which can be compared to age-dependent normative data for males and females.

Validity of the 1 minute stage version of the 20 meter shuttle run to predict VO2max in adults was established by Léger et al. , who compared the maximal shuttle run speed to VO2max attained during a multistage treadmill test.

In addition, blood pressure and oxygen saturation will be assessed prior to testing in order to detect potential contraindications. Resting pulse and recovery pulse (2 minutes after test) will be measured and heart rate will be continuously recorded during test. Furthermore, participants will be instructed to rate their perceived physical exertion before and after test using the Borg scale.

### 2.4.3 SenseWear Mini armband

The SenseWear Mini armband is a small, lightweight and wireless multisensory activity monitor developed by Bodymedia (Pittsburgh, Pennsylvania, USA), which integrates motion data from a three-axis accelerometer along with several other physiological sensors such as heat flux, skin temperature and galvanic skin response. Validity was established by Johannsen et al. comparing energy expenditure estimates of the SenseWear Mini armband against the criterion method ‘Doubly-Labelled-Water’ in healthy adults.

The subjects will be instructed to wear the SenseWear Mini armband on the upper left arm (triceps area) for 7 consecutive days, including while sleeping, with the exception of the time spent on personal hygiene (23 hours per day). Reliability of this assessment period has been previously shown .

For recording non-wearing periods, such as water activities and showers, participants will be asked to keep a diary. The physiological data collected by the armband’s sensors will be processed by specific algorithms (professional software V.7.0, algorithm V.2.2.4) to calculate participants’ daily active energy expenditure, physical activity duration at different intensities and number of steps. Gender, age, height, weight, smoking status and handedness will also be considered in these calculations.

The output of a healthy person created by the SenseWear Mini software is presented in Figure 2. The variables of interest are marked with a circle. Furthermore, it can be seen that that the Mini armband was worn on 5 consecutive days, while the large numbers represent the average over these days.

**Figure 2:** SenseWear Mini output of a healthy person.

## 2.5 Data collection, management and retention

A member of the study team will contact employees from selected companies around Basel. Participation is voluntary and can be revoked at any time. There is no disadvantage for individuals that do not take part in the study.

To ensure a standardized process, measurements will be carried out always by the same study nurses trained for this purpose. For data collection and management, data will be anonymized and participants will be identified by a study number. Test results will be transmitted to the participants after all investigations have been performed.

All study related records and informed consent documents will be retained in the Clinic of Internal Medicine at the University Hospital of Basel as long as required by the applicable Swiss regulatory requirements (10 Years). Moreover, monitoring visits, audits and regulatory inspections will be granted direct access to the obtained data.

## 2.6 Data analysis

For the specific analysis of occupational activity parameters, working hours will be defined as effective time spent at work, whereas the way to work and breaks in between will not be taken into account. Participants will be instructed to keep a diary for documenting working time.

### Primary endpoints

Primary endpoints will include the following measurements of the SenseWear Mini armband during working time:

1. - Average daily active energy expenditure [cal]
2. - Average daily physical activity duration at different intensities [min]

(Low (<3.0 METs), middle (3.0-6.0 METs), high (6.0-9.0 METs) and very high (>9.0 METs))

1. - Average daily number of steps
2. - Graphs with plotted distribution of physical activity periods

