# Introduction

## 1.1 Background

Regarding occupational rehabilitation, a balance between workload and individual’s work capacity is required for returning to work successfully after an injury or illness. Therefore, it is of great value to evaluate a wide range of physical work requirements and to assess employee’s work capacity across occupational categories. Although several approaches have been made in this regard, there are few objective data available so far and no established thresholds exist. One reason could be that objectifying workload and work capacity is methodically challenging because of their multidimensional nature .

Physical activity is defined as any bodily movement produced by skeletal muscles resulting in energy expenditure *.* In classical work physiology, energy expenditure was therefore considered as basis for assessing the amount of workload *.* However, the energy cost of physical activity may not necessarily be equivalent to body movement . For that reason, modern concepts include also other aspects reflecting the severity of manual work. The ‘Dictionary of Occupational Titles’ (DOT), developed by the U.S. government, classifies professions into five categories (sedentary, light, medium, heavy, very heavy) based on the amount of energy expended as well as on the intensity and duration of lifting or carrying during work . Though, the DOT classification has not been based on quantitative work-related analyses, but rather on consensus meetings of experts. Furthermore, its validity has not been established.

Work capacity can be assessed using functional capacity evaluations (FCEs), which measure the ability of subjects to perform specific activities . Worldwide, there are various FCE protocols available being job specific , pathology specific or of a more general type. Soer et al. applied an evaluation system consisting of 12 work-related tests to establish functional capacity in healthy employees . The assessment included various lifting and energetic exercises as well as coordination tasks. From the test results, normative FCE values were acquired for each DOT-category, which can be compared to patient data in order to make work recommendations.

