### 2.6.2 Secondary endpoints

1. - IPAQ: Total and subtotal domain specific scores (work, leisure-time, transport,

domestic & garden [MET-min/week] and sitting time [min/week])

1. - SF-36: Total and subtotal domain specific scores (9 domains)
2. - VAS: Scores of perceived work and leisure-time physical exertion and effort
3. - Borg scale: Values of rated physical exertion at work (midday and evening)
4. - Results of the 20 meter shuttle run: predicted VO2max [METs]
5. - Results of the SenseWear Mini armband in recreation: activity and energy scores

as listed above

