### 2.6.3 Statistical analysis

Statistical analyses will be done using the software R (version 2.15.1) and IBM SPSS Statistics (version 19.0). Statistical significance will be acquired if a p value of less than 0.05 is attained.

Data will be presented by descriptive statistics within occupational groups. Cross tables are reported as counts and percentages. Ordinal variables are reported as median and Interquartile range (IQR). Metric variables are reported as mean and standard deviation (SD).

To evaluate primary endpoints, linear regressions will be performed. Independent variable is “occupational group”, dependent variables are “average daily active energy expenditure”, “average daily physical activity duration” and “average daily number of steps”. Optionally, personal and job related factors can be included in the regression analyses as covariates. If appropriate, data will be log-transformed. Regression results will be presented as differences of means between “occupational categories” with corresponding 95% confidence intervals (C.I.) and p-values. In case of logarithmic distributed data, geometric mean ratios will be presented.

To evaluate secondary endpoints, linear regressions will be conducted. In case of ordinal variables, non-parametric methods will be applied.

Furthermore, the mean and individual time courses of physical activity periods will be plotted for all primary and secondary variables.

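### The low-intensity band of the primary activity-duration endpoint has no lower limit, so sitting at work, and sleep in the recreation scores, counts as physical activity

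*Protocol*

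**What the plan says.** Section 2.6.1 (Primary endpoints) opens with "Primary endpoints will include the following measurements of the SenseWear Mini armband during working time" and lists "Average daily physical activity duration at different intensities [min" among them, in minutes. The bands are "Low (<3.0 METs), middle (3.0-6.0 METs), high (6.0-9.0 METs) and very high (>9.0 METs". Middle, high and very high each have a lower limit; low has none.

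Section 1.1 gives the Protocol's own definition: "Physical activity is defined as any bodily movement produced by skeletal muscles resulting in energy expenditure".

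Section 2.6 restricts working hours to effective time at work, leaving out the commute and breaks. Section 2.6.2 adds, as a secondary endpoint, "Results of the SenseWear Mini armband in recreation: activity and energy scores", using the same list as for work. Section 2.4.3 has the armband worn "for 7 consecutive days, including while sleeping", 23 hours a day.

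Section 2.6.3 regresses "average daily physical activity duration" on occupational group without naming a band. Log transformation is allowed where appropriate, and then "In case of logarithmic distributed data, geometric mean ratios will be presented".

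Sitting is recorded as a separate quantity only in the self-report questionnaire (IPAQ, sections 2.3.3 and 2.6.2). The text gives no sedentary or sleep category for the armband.

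**The concern.** An endpoint labelled as activity duration should not rise when a person moves less. With no floor on the low band, a minute of motionless sitting scores the same as a minute of light manual work. The band therefore conflicts with the definition in section 1.1.

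Two things are at stake. First, one component of a primary endpoint carries no information beyond the other bands and the hours worn, yet would be reported under the name of physical activity. Read alone, it can suggest that desk workers are the more active at low intensity. Second, the same band in recreation takes in sleep unless a rule removes it. That weakens any use of it as non-work physical activity, for example in the second hypothesis of section 1.3, which relates exercise capacity to work and non-work activity.

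**Working it through.** **The plan's own figure.** The only computed figure nearby is the power statement in section 2.6.4, for active energy expenditure: 100 per group, difference 500 kcal, SD 730 kcal, two-sided 5%. The standard error is 730 × √(2/100) = 103.2, and 500/103.2 = 4.84. Power is Φ(4.84 − 1.96) = 0.998, so the stated power above 90% is reproduced. It does not concern the duration bands, which have no power calculation.

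**Step 1: the low band is a complement.** Let W be armband wear time within effective working hours. Every worn minute has a MET value and falls in some band, so

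low = W − (middle + high + very high).

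The one exception is a minute at exactly 6.0 METs, which the printed limits place in both middle and high.

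**Step 2: what this does to group differences.** Fix W at 480 min (an assumed 8-hour day) and simulate illustrative minutes for 100 subjects per group:

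| Comparison | Difference, three upper bands together | Difference, low band |
|---|---|---|
| High- minus low-activity group | +131.2 min | −131.2 min |
| Middle- minus low-activity group | +49.7 min | −49.7 min |

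The sizes follow from the assumed inputs; the mirror image does not. If W varies, the difference in low equals the difference in W minus the difference in the upper bands, so hours worked enter as well.

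**Step 3: sitting against light work.** Take two workers with W = 480 min and 40 min at or above 3.0 METs (both assumed). Each has 480 − 40 = 440 min in low, whether those minutes were spent sitting still or in light tasks.

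**Step 4: recreation.** Worn time is 23 × 60 = 1380 min a day. Assume 420-540 min of work, which leaves 840-960 min, and 360-480 min of sleep. Sleep is then between 360/960 = 38% and 480/840 = 57% of worn non-work time on a working day. On a day off it is 360/1380 = 26% to 480/1380 = 35%. All of it falls below 3.0 METs, so its share of the low band is at least as large.

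**Step 5: side check on zeros (conditional).** Suppose a subject has no minutes in an upper band on a given working day with probability q, independently over five days (assumed). The average is then exactly zero with probability q⁵: 3%, 33%, 59% and 77% for q = 0.5, 0.8, 0.9 and 0.95. The Protocol gives no value for q. Where zeros occur, log(0) is undefined. Adding a constant does not solve this: in a simulation with 50% against 40% zeros and the same distribution of positive values, the geometric mean ratio was 1.84, 1.46 or 1.19 for constants of 0.01, 0.1 or 1 min.

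**The case against.** The case on the other side is that the flaw is narrow and mostly one of labelling. Much of that stands.

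- **A total over the bands.** A reader might infer from section 2.6.3 that the four bands are added up, which would give every worker simply the hours worn. The documents do not support this. Sections 1.2, 2.4.3 and 2.6.1 all speak of duration at different intensities, and the unqualified name in 2.6.3 is most naturally shorthand for that. The wording still deserves one clarifying sentence.
- **The first hypothesis coming out reversed.** This could apply only to the low band read in isolation. Beside the other bands, more time below 3.0 METs in desk workers agrees with the hypothesis. Nor do the documents say that the lower two occupational groups differ mainly in posture.
- **Upper bands mostly zero and impossible to analyse.** The Protocol gives no figure for time above 6 or 9 METs. Logging is optional, and dropping zeros is planned nowhere. Zero handling may also sit in a SAP, which was not available for this check.
- **Sleep.** Wearing the armband at night does not by itself mean that sleep is scored as recreation, and only a secondary endpoint is involved. But the text has no rule that removes it. The sample output in Figure 2 was not available for this check; if it marks a sleep or sedentary variable, the endpoint text should say so.

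The objection does not remove the core. The cut-offs are stated in the Protocol for a primary endpoint, and followed as written they count stillness as activity.

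**Conclusion.** The point holds for the low band. As defined, it contradicts section 1.1, is fully determined by worn working time and the other bands, and cannot tell sitting from light work. In recreation it also takes in sleep unless a rule is added. The 38-57% share of worn non-work time on working days rests on assumed work and sleep hours.

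The reach is limited. Active energy expenditure, which section 2.6.4 calls the most important primary endpoint, is untouched. So are steps, the bands from 3.0 METs upward (apart from the shared limit at 6.0) and the power statement. The zeros are a risk that depends on data the Protocol does not give, not an error the plan commits to.

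**What to change.** 1. In section 2.6.1, split the band below 3.0 METs into sedentary and light, for example below 1.5 and 1.5 to <3.0 METs, and do not count sedentary time as physical activity. The 1.5 cut-off is a suggestion and is not in the Protocol.
2. Make the limits exclusive: 3.0 to <6.0, 6.0 to <9.0, and ≥9.0 METs.
3. In section 2.6.2, exclude sleep from the recreation durations and say how it is identified.
4. In section 2.6.3, state that each band is analysed separately and not as a total over all bands.
5. Conditionally: if some subjects have zero minutes in an upper band, do not log-transform that band. Analyse it on the untransformed scale or as any versus none.

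The cost is one more cut-off in processing data that are collected anyway, a rule for sleep, and one more band to report. Recruitment, measurements and sample size stay as they are.

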## 1.2 Specific aims

The primary aim of this study is to investigate healthy employees in Switzerland regarding active energy expenditure, physical activity duration at different intensities and the distribution of medium- and high-intensity activity periods of more than ten minutes during a normal working day with focus on differences between occupational categories. Furthermore, the association between physical activity and exercise capacity will be examined.

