### 1.3.3 Better trained subjects (with a higher aerobic capacity) show longer periods of medium- and high-intensity activity than untrained individuals.

## 1.4 Potential significance

This study is expected to provide detailed information about physical work requirements and performance criteria of different job categories. This may be valuable regarding treatment and professional reintegration after an injury or illness, since up to now no established thresholds exist. Objective workload data might improve clinicians’ recommendations for a successful return to work.

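### The activity-period part of the primary aim has only a graph as its endpoint, and hypothesis 1.3.3 names no predictor model, so as specified the plan gives no group estimate for the one and no stated test of the other

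*Protocol*

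**What the plan says.** Section 1.2 names three things to be studied with a focus on differences between occupational categories: active energy expenditure, activity duration by intensity, and the "distribution of medium- and high-intensity activity periods of more than ten minutes during a normal working day". Section 1.1 gives the reason for the third: absolute values may not tell the whole story, so the pattern of activity is to be evaluated too.

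Hypothesis 1.3.3 says that subjects with higher aerobic capacity "show longer periods of medium- and high-intensity activity than untrained individuals".

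Section 2.6.1 lists four kinds of primary endpoint during working time: active energy expenditure, minutes in each of four MET bands, steps, and "Graphs with plotted distribution of physical activity periods". Section 2.6.2 adds predicted VO2max and the same armband scores for recreation.

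In section 2.6.3 the primary regressions are set out as follows: "Independent variable is “occupational group", and "dependent variables are “average daily active energy expenditure”, “average daily physical activity duration” and “average daily number of steps". Secondary endpoints are also to be analysed by linear regression, without named predictors. For activity periods, the plan is that "the mean and individual time courses of physical activity periods will be plotted for all primary and secondary variables".

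**The concern.** A graph is not a per-subject outcome. It has no unit, cannot enter the planned regression, and produces neither a difference between groups nor an interval around one. Yet section 1.2 asks for a comparison between groups, and 1.3.3 is a directional hypothesis about period length.

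Two things are at stake. First, a named component of the primary aim would be reported as pictures only. Secondly, if somebody later turns the pictures into numbers, then the minimum length, the intensity cut-off and the treatment of short interruptions would all be chosen after the data are in hand, at a 5% significance level.

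**Working it through.** **The plan's own figure.** The only calculation in the protocol is the power statement in section 2.6.4 (100 per group, difference 500 kcal, SD 730 kcal, two-sided 5%). The standard error is 730 × √(2/100) = 103.2, so the standardised difference is 500/103.2 = 4.84. Power is about Φ(4.84 − 1.96) = Φ(2.88) = 99.8%, which agrees with the stated figure of over 90%. It concerns energy expenditure only. The protocol gives no variable, SD or effect size for activity periods, so no power can be computed for them.

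**Tracing the period component.**

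| Step | Section | What is fixed for activity periods |
|---|---|---|
| Aim | 1.2 | Distribution, over ten minutes, medium and high intensity, compared between categories |
| Hypothesis | 1.3.3 | Longer periods in better trained subjects; no ten-minute threshold |
| Armband outputs | 2.4.3 | Energy expenditure, duration by intensity, steps; no period measure |
| Primary endpoint | 2.6.1 | A graph; no unit, minimum length or intensity cut-off |
| Secondary endpoints | 2.6.2 | Recreation scores mirroring the primary list; no period measure added |
| Regression outcomes | 2.6.3 | Energy expenditure, duration, steps; no period measure |
| Regression predictor | 2.6.3 | Occupational group; VO2max not named |
| Handling of periods | 2.6.3 | Plotting |

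The ten-minute criterion does not reappear after section 1.2.

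**Can an existing numeric endpoint stand in?** There are 1 (energy expenditure) + 4 (MET bands) + 1 (steps) = 6 numeric primary endpoints. Take two hypothetical subjects, each with 40 minutes per working day in the 3.0–6.0 MET band:

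| | One 40-minute period | 40 isolated single minutes |
|---|---|---|
| Minutes in the band (section 2.6.1) | 40 | 40 |
| Minutes in periods over ten minutes | 40 | 0 |
| Longest period, minutes | 40 | 1 |

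If intensity and steps are also equal, all six endpoints coincide. Total duration does not separate sustained from scattered activity, which is the distinction that section 1.2 draws by listing the two separately.

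**Why an interruption rule is needed.** Suppose that 20 minutes of work contain one minute below 3 METs, splitting them into 9 + 1 + 10. With no tolerance, neither part exceeds ten minutes and the subject scores 0. With a one-minute tolerance there is a single period of 20 minutes. The definition alone can move the result from 0 to 20.

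**The case against.** The strongest case on the other side has four parts.

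- **The component is descriptive.** Section 1.2 speaks of investigating a distribution, no hypothesis predicts a group difference in periods, and section 2.6.4 ranks energy expenditure as the most important endpoint. Plots by group are a legitimate description. This stands in part: a p-value is not obligatory. But the stated focus on differences between categories calls for at least an estimate with its precision.
- **The analysis plan may define the derivation.** Interruption tolerance and similar rules are commonly left to it. That is fair for the details. However, the protocol does not leave the endpoint open. It fixes a graph and lists the regression outcomes without any period measure.
- **Hypothesis 1.3.3 may mean total time.** If longer periods means more minutes at those intensities, the minutes exist at work and in recreation, predicted VO2max is a secondary endpoint, and section 2.9 reserves the relation between exercise capacity and activity for a second publication. A reader might infer from the gap that no effect size could ever be had for 1.3.3; the documents do not support that. Still, section 1.2 separates duration from periods, and on either reading section 2.6.3 states no model on VO2max.
- **The data permit repair.** A reader might also infer that the question is beyond estimation altogether. It is not: the planned individual time courses imply time-resolved recordings. The gap lies in the specification.

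Two further inferences should be avoided. The ten-minute threshold belongs to section 1.2 and not to 1.3.3. And the component cannot be called a third of the primary aim, because the protocol gives its parts no equal weight.

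**Conclusion.** The point holds as a break between aim, endpoint and analysis. As specified, the protocol provides no per-subject measure of activity periods, hence no between-group estimate or confidence interval for that component of the primary aim, and it states no test of hypothesis 1.3.3. None of the six numeric primary endpoints substitutes for such a measure. Energy expenditure, duration, steps and the power statement are unaffected. The size of the loss cannot be put as a number, because the documents give no distribution of period lengths.

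The conclusion assumes that medium intensity in section 1.2 corresponds to the middle band (from 3.0 METs) in section 2.6.1, and that periods in 1.3.3 carries the same sense as in section 1.2, as distinct from total duration. If the second assumption is dropped, the defect for 1.3.3 shrinks to an ambiguous term and an unnamed predictor, but it does not vanish.

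**What to change.** **Section 2.6.1.** Replace the graph as an endpoint with one principal measure per subject: average daily minutes, during working time, spent in periods of more than ten consecutive minutes at 3 METs or more. State the interruption rule, and how a period is treated when it meets a break, since section 2.6 excludes breaks from working time. Count subjects with no such period as zero. Keep the number of periods and the graphs as supportive description. Mean period length is a poor principal measure because it is undefined for anyone with no period.

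**Section 2.6.3, group comparison.** Compare the measure between occupational groups and report differences with 95% CIs, using a method that tolerates many zeros, such as bootstrap intervals or a two-part model. The planned linear model with optional log transformation does not suit an outcome with a mass at zero.

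**Section 2.6.3, hypothesis 1.3.3.** Name a period-length measure without the ten-minute restriction, for example the longest daily period at 3 METs or more, at work and in recreation. Regress it on predicted VO2max, adjusted for occupational group, age and sex.

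**Cost.** A small derivation script, some wording in two sections, and a few more outcomes to label as secondary or supportive so that they do not lengthen an already multiple primary list. The change relies on time-resolved armband data. Section 2.4.3 lists only daily outputs and gives no recording interval, so the export should be confirmed, ideally in the planned pilot of 15 persons.
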